## Discussion

Examining the implementation process of clinical practices has become an essential part of evaluating the impact of such a practice [24]. Often healthcare policies make recommendations about what to do without including specific guidance about how to address system-level implementation barriers. Along these lines, the STORM policy notice has allowed VAMCs and individual providers to determine whether or how to go about conducting case reviews and whether or not to use the STORM dashboard. Although OMHSP has offered general guidance, webinars about STORM’s availability, and guidance through the policy notice itself on how to carry out the case reviews (e.g., identifying a POC, suggesting staff to be involved, establishing a specific case review note), providing in-depth facilitation to all VAMCs is not practical. Also, there are several models that VAMCs could use to incorporate data-based case reviews into practice, and it is likely that VAMCs will vary in the models they use based on their local environment. Complicating matters further, VA, the largest integrated healthcare system in the US, includes facilities that vary widely on myriad factors such as size, location, patient populations, resources, services offered, and organization, all of which could affect implementation of the policy notice. Local variability has been seen in other related national initiatives, such as implementation of buprenorphine for the treatment of opioid use disorder [38–40].

OMHSP is interested in understanding whether and how the case reviews of patients at very high risk of opioid-related SAEs get incorporated into practice and the factors that affect the ability of VAMCs to carry out such case reviews effectively. Understanding whether including facilitation (vs. no facilitation) in the policy notice increases facility compliance will inform future policy development. Testing the effect of adding new patients into the STORM risk group for whom case reviews are required will yield insights regarding which patients should be targeted for case reviews to achieve the desired reduction in opioid-related SAEs. The implementation evaluation will complement the analysis of changes in opioid-related SAEs over time and across randomization arms. We will be able to learn which implementation strategies are most effective in supporting case reviews, and how that relationship differs between the facilitation (which itself is an implementation strategy) and no facilitation arms. We will also be able to learn which barriers and facilitators, using CFIR, are most salient across the four arms. Finally, combining data on implementation strategies and barriers at such a large scale could advance implementation science by showing which strategies are naturally best suited to address certain barriers.

There are important limitations that also must be considered. Most importantly, this intervention is occurring in the context of many other national, regional, and local opioid safety initiatives emerging or already in place. The randomized design is an important method to address this concern, and the ERIC survey and qualitative interviews will elucidate how other initiatives impact particular facilities during the course of the trial. Second, any survey targeting employees and providers will have challenges achieving an adequate response rate, especially given the length of the survey and inability to incentivize respondents. However, the previous use of the ERIC survey in a similar initiative achieved a good response rate (74%) and found that respondents who started the survey completed the survey, with no bias towards endorsement of strategies presented earlier in the survey [30]. Finally, the evaluation is at the facility level, meaning there will be ERIC data on no more than 141 sites. Power is thus limited to detect small differences across arms and to control for all the potentially relevant organizational covariates. However, we are maximizing the chance of finding an effect by using a rigorous randomized approach that includes all VAMCs.

In sum, the evaluation of implementation factors will provide valuable insights into how VAMCs implement a policy designed to reduce opioid-related SAEs among Veterans and will identify types of implementation strategies that are associated with successful implementation. The resulting data from the evaluation described here will help OMHSP and other VA decision makers prioritize which types of implementation strategies to recommend and use in future policy rollouts and implementation initiatives.

### Trial status

This evaluation was funded as a VA Health Services Research and Development Service Directed Project in April of 2016 and has proceeded in two phases. In the planning phase (April 2016–March 2017), the implementation evaluation team met biweekly with representatives from OMHSP and PEPReC to inform the language of the policy notice, to determine the design and timing of the arms to be included in the stepped-wedge randomized evaluation, and to align the activities that would be completed by each partner (OMHSP, PEPReC, and our implementation evaluation team) leading up to and following the release of the policy notice. These biweekly discussions have continued since transitioning to the active evaluation phase (April 2017–March 2020) and have maintained awareness and alignment of activities across each partner.

The implementation evaluation activities were approved by the Veterans Affairs Pittsburgh Healthcare System Institutional Review Board on March 6, 2017. The policy notice VA NOTICE 2018-08 CONDUCT OF DATA-BASED CASE REVIEWS OF PATIENTS WITH OPIOID-RELATED RISK FACTORS, was released to the field in March of 2018, at which time VAMCs (*N* = 141) were randomized to one of four evaluation arms. Collection of the ERIC survey data for aim 1 began October 1, 2018 and closed December 16, 2018, at which time OMHSP began reaching out to VAMCs that have not reached the 97% case review completion rate target. If survey responses are received after that date, they will be flagged as being received after facilitation began at some sites and will be explored to determine whether they differ from responses received earlier. Recruitment of VAMCs for CFIR interviews (aim 2) will begin in February of 2019.

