## Methods

### Overview of STORM evaluation randomization design

All VAMCs have been randomized (March 2018) to STORM rollout arms that reflect two independent variables: (1) whether a VAMC receives additional oversight and assistance (i.e., facilitation: yes or no), and (2) the timing of when a VAMC’s group of patients to be reviewed will be expanded from the top 1% to the top 5% of STORM risk scores (i.e., risk group expansion: 9 or 15 months following the release of the policy notice) (Fig. 1). For the “facilitation” variable, VAMCs are randomized to one of two policy notices, both requiring the completion of data-based case reviews of patients identified by STORM as having a very high risk of SAEs. One policy notice specifies that, if fewer than 97% of the required case reviews have been conducted within 6 months of when the policy notice was released, the VAMC will be required to receive additional facilitation (i.e., outside coaching), which includes creating an action plan to implement case reviews and undergo additional oversight by OMHSP (the “facilitation” arm). The other policy notice includes no mention of additional oversight, action plans, or facilitation if the 97% case review metric is unmet (the “no facilitation” arm).

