For the “risk group” variable, the pool of patients for whom case reviews are required will be expanded using a stepped wedge design. For a baseline period lasting 8 months following the release of the policy (*T*_0_), all VAMCs will be required to review all patients in the top 1% of STORM risk scores. At the beginning of month nine, the pool will be expanded at half of the VAMCs, at random, to include patients with STORM risk scores in the top 5% (*T*_1_). This step will last 6 months, at which time the pool of patients will be similarly expanded for the remaining VAMCs (*T*_2_). The change in risk group will occur “behind the scenes,” such that facilities are not aware which arm they are in or that the change is taking place. Varying whether the policy involves additional oversight and facilitation will enable an assessment of whether a policy that includes concrete repercussions for non-compliance is more effective than one that does not; varying the risk group defining which patients are required to have their cases reviewed will enable an assessment of the level of risk at which STORM-facilitated case reviews are associated with reduced risk of opioid-related SAEs. In both cases, there is equipoise about which arm will result in improved outcomes.

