##### Data collection

Approximately 6 months following the release of the policy notice, the POC for the policy notice from every VAMC (*N* = 141) will be invited to complete the ERIC survey on behalf of their facility. The survey will be web-based and the web platform will ask respondents for consent before they complete the survey. To encourage high participation, OMHSP will first send an email to POCs alerting them that they will be contacted by the implementation evaluation team and asking that they consider participating in the evaluation. The importance of having all VAMCs represented in the analysis will be emphasized. The following week, the implementation evaluation team will send each POC an email that describes the ERIC survey, includes a facility-specific link to the online survey, and provides access to printable copy of the survey. POCs will be advised to review the survey in its entirety prior to completing the online version and to obtain input from others at their VAMC as needed. Study staff will follow up with POCs by email, followed by telephone calls, and/or the VA’s instant messaging system, as needed. Reminders to complete the survey will also be made at the monthly Community of Practice calls hosted by OHMPSP during the recruitment period.

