### Data analysis

#### Aim 1

ERIC survey responses will first be summarized by computing a cross tabulation of use of each of the 68 strategies in the past 6–8 months (yes/no) by the two facilitation randomization arms (facilitation or no facilitation). The proportion of strategies used within each cluster of strategy types and the total number of strategies implemented in the past 6–8 months will also be computed and described by arm. This process will be repeated to describe the number and type of strategies that were implemented as a direct response to the policy notice. Primary analyses for aims 1a and 1b will be based on whether the strategy was used in the past 6–8 months. As a sensitivity analyses, we will repeat these analyses based on whether the strategy was implemented as a direct response of the policy notice, which will be indicated in the survey responses.

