#### Aim 1b

The primary analysis for aim 1b will estimate the association between number of implementation strategies used and completion of case reviews at *T*_0_ + 6 months. If enough VAMCs meet the 97% target completion rate, we will analyze the data using logistic regression for the outcome of meeting the target rate; otherwise, we will model the proportion of case reviews completed. The outcome will be modeled using a generalized linear model with logit link and binomial family. This strategy will appropriately model the case review completion rates as being restricted between 0% and 100% and is equivalent to logistic regression for binary (yes/no) outcomes. For these analyses, the number of implementation strategies used will be the independent variable and will be coded as either continuous or categorical. Because difficulty in completing case reviews could increase as volume of very high-risk patients increases, we will include the number of very high-risk patients at each facility as a predictor along with the other facility variables.

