Additional analyses will assess the association between the type of implementation strategies used and the case completion rate. We will assess the association between each individual strategy and case review completion in individual regression analyses. We will also assess the relationship between the percent of implementation strategies used within each cluster of strategy types and case review completion rates. Because we have adapted the ERIC survey for this evaluation, we will conduct confirmatory factor analyses to verify that the original clusters were maintained. If the factor analysis does not confirm the original clusters, we will describe the resulting strategy type factors and utilize summary scores based on the new factors. Finally, we will assess whether the overall number of implementation strategies used mediates the relationship between randomization arm and case review completion rate. We will test mediation using the bootstrapping methods of Preacher and Hayes [35]. These methods will allow for the direct estimation and testing of mediation and do not make any distributional assumptions (such as normality) regarding the variables or the test statistic. Analyses are based on taking a large number of bootstrap samples with replacement from the original data and estimating effects for each sample. The mean estimated effect and empiric confidence intervals are computed across all samples. Furthermore, because inferences do not depend upon large-sample theory, this method can be used for data with smaller sample sizes.

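### The aim 1b strategy count runs past the T0+6-month outcome date by an amount that depends on response date, so strategies added after a shortfall can be counted as predictors or mediators of it

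*Protocol article*

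**What the plan says.** All places are in the Protocol article.

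- **Start of the clock.** Under Trial status, the notice "was released to the field in March of 2018, at which time VAMCs" were randomized. The day in March is not given. Under Overview of STORM evaluation randomization design, T0 is introduced with "For a baseline period lasting 8 months following the release of the policy".
- **Outcome.** Under Aim 1b, the primary analysis concerns "completion of case reviews at *T*_0_ + 6 months". This matches the 97% target, which applies to reviews "conducted within 6 months of when the policy notice was released".
- **Exposure.** Under Data analysis, Aim 1: "Primary analyses for aims 1a and 1b will be based on whether the strategy was used in the past 6–8 months". The survey item counts back from the time of answering. Neither the item nor the analysis limits the count to strategies in place by T0+6.
- **Survey timing.** Data collection plans the invitation for "Approximately 6 months following the release of the policy notice". Trial status gives the actual window: "Collection of the ERIC survey data for aim 1 began October 1, 2018 and closed December 16, 2018".
- **Mediation.** Under Aim 1b: "we will assess whether the overall number of implementation strategies used mediates the relationship between randomization arm and case review completion rate". No outcome time is restated there; T0+6 is the natural reading.
- **Timing safeguard.** Under Trial status, responses received after 16 December are to be flagged and compared with earlier ones, because outreach to facilities below target began then. Nothing is said about response date within the main window.

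**The concern.** An exposure meant to explain an outcome should describe what happened before it. Here the recall window ends after the outcome date for every respondent, and how far after depends on when the facility answered. A facility that learned in September that it was below 97% had reason to add strategies in the autumn and could then report them. Low completion would in that case produce a higher strategy count, which pulls the estimated slope down and could hide a real benefit or suggest a harmful one.

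Mediation is the more exposed analysis, because its interpretation needs the mediator to precede the outcome. Describing aim 1b as an association does not fully answer this: the Discussion expects the results to show which strategies work best and to guide which ones are recommended in future rollouts.

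**Working it through.** The plan states no figure on this point, so there is none to reproduce. The check is calendar arithmetic, then a look at how far the size of any bias can be known.

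**Inputs.** Release R: 1 to 31 March 2018 (Trial status; day not given, so the whole month is used). Outcome date O = R + 6 months. Response date S: 1 October to 16 December 2018 (Trial status). Look-back w: 6 or 8 months (survey item).

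**Formulas.**
- Delay = S − O.
- Share of recall window after the outcome = (S − O) / (length of w in days).
- Start of outcome period not covered = (S − w) − R, if positive.

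**Outcome date.** R = 1 March gives O = 1 September; R = 31 March gives O = 30 September.

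| Response | Look-back, window start | Delay (days) | Share of window after O | Outcome-period days missed |
|---|---|---|---|---|
| 1 October | 6 months, 1 April | 1–30 | 1/183 to 30/183 = 1–16% | 1–31 |
| 1 October | 8 months, 1 February | 1–30 | 1/242 to 30/242 = 0–12% | 0 |
| 16 December | 6 months, 16 June | 77–106 | 77/183 to 106/183 = 42–58% | 77–107 |
| 16 December | 8 months, 16 April | 77–106 | 77/244 to 106/244 = 32–43% | 16–46 |

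The outcome period is 183–184 days. Every response follows the outcome date whatever the March release day, but the overlap moves from trivial to large across the survey window.

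**End of October.** For a 31 October response the delay is 31–60 days. The 6-month window (from 30 April, 184 days) gives 31/184 to 60/184 = 17–33%. The 8-month window (from 28 February, 245 days) gives 31/245 to 60/245 = 13–24%.

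**Size of the bias.** The document gives neither the number of strategies added after month 6 nor the share of facilities below 97%, so both must be assumed. The illustrative simulations use 80 facilities with mean 25 and SD 14 strategies (Power and sample size) and let every facility below 97% add strategies before answering.

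- *90% baseline completion, facility log-odds SD 1, 20–119 reviews per facility (assumed), 6 added:* estimated slope falls from 0.32 to 0.24 and power from 76% to 51%. With no true effect, false positives rise from 7% to 13%.
- *70% baseline, same settings:* slope 0.30 to 0.28, power 82% to 74%, false positives essentially unchanged.
- *Facility SD 0.9, true slope 0.35 log-odds per 14 strategies:* at 50%, 70% and 80% completion, 98–100% of facilities are below 97%. The slope stays near 0.30 with 0, 6 or 10 added, and power is essentially unchanged. At 90%, power goes from 87% to 77% (6 added) to 67% (10 added).

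The reason is simple. If nearly all facilities are below 97%, the added strategies are almost a constant shift and the slope barely moves. If facilities are split around 97%, the shift is tied to the outcome. The plan's logistic analysis of meeting the target is reserved for the case where enough facilities meet it, which is nearer the second situation.

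**The case against.** The strongest defence is that the survey is retrospective. A question about a six-month period is naturally asked at or after its end, and the plan intended to ask it at about six months. Ascertaining exposure after the outcome is not the same as exposure occurring after it: for a 1 October response, 84–100% of the window precedes T0+6. Only strategies newly adopted after September can cause harm, and the document does not say how many there were. The survey also closed as outreach to facilities below target began, so facilitation itself does not contaminate the main window. All of this stands. It limits the concern but does not remove it, because later responses carry a large post-outcome share. The sensitivity analysis of strategies used in direct response to the notice does not order them in time.

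Four stronger readings are tempting, and the documents support none of them.

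- *That the whole exposure postdates the outcome.* Much of the recalled activity precedes it.
- *That the loss of overlap is typically as large as for a 16 December response with a 6-month look-back.* That is the extreme case, and the distribution of response dates is not given.
- *That the bias is known to differ by arm.* Only one arm's notice announced facilitation and oversight, so it is plausible, but neither the document nor the simulations above show it.
- *That a drop from a true slope of 0.35 to an estimate near 0.30 measures reverse causation.* That gap appears with no strategies added, because variation between facilities attenuates the slope.

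**Conclusion.** The concern holds in a limited form. For any release day in March 2018, the primary aim 1b exposure extends beyond the outcome date, by 0–16% of the recall window at the start of the survey and 32–58% at its end. Late windows also miss the first 16–107 days of the outcome period. The only safeguard begins after 16 December. If facilities below 97% added more strategies before answering than the others did, the slope is biased downward. The size cannot be fixed from the document and runs from near nil to substantial, depending on the share of facilities below 97% and the number of strategies added.

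This rests on reading T0+6 as release plus six months, which the 97% target supports, and on the mediation analysis using the same outcome time.

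A reader might infer that the primary outcome must move to the end of month 8. The calendar does not support that as a cure. Month 8 ends between 1 and 30 November, inside the survey window, so a 16 December response would still come 16–45 days after it. The move would also detach the outcome from the policy's six-month target after survey collection had closed.

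**What to change.** 1. Keep completion at T0+6 months as the primary aim 1b outcome.
2. Include days from T0+6 to survey response as a covariate in the aim 1b and mediation models. This removes average drift in the count with response date. It does not remove a link between shortfall and added strategies, so it is not enough alone.
3. Extend the comparison described under Trial status to a pre-specified sensitivity analysis restricted to early responders, for example those answering in October. Report its overlap openly: an end-of-October response can still have 13–33% of its window after the outcome date.
4. Optionally add end-of-month-8 completion, adjusted for month-6 completion, as a secondary analysis, noting that responses after that date still postdate it.
5. Report mediation of the T0+6 outcome as exploratory and not causal, and state the order-in-time limitation.

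Cost: one more model term, some wording, and a smaller early-responder subset with less precision, possibly below the 70–90 facilities considered under Power and sample size. The optional analysis needs completion extracted at one more date.

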## Abbreviations

CFIR: Consolidated Framework for Implementation Research
CHERP: Center for Health Equity Research and Promotion
ERIC: Expert Recommendations for Implementing Change
OMHSP: Office of Mental Health and Suicide Prevention
OTG: Opioid Therapy Guidelines
PEPReC: Partnered Evidence-Based Policy Resource Center
POC: Point of contact
STORM: Stratification Tool for Opioid Risk Management
VAMC: Veterans Affairs Medical Centers
